### Procedure

Individuals first provide signed consent to receive ECT as part of their care. Subsequently, at the screening visit, all participants provide written informed consent in adherence with Good Clinical Practice guidelines before initiation of any study related procedures. Participants then undergo a full medical work-up to ensure ECT and ketamine treatment suitability, which includes a medical history, physical examination*,* height, weight and vital signs measurements, 12-lead electrocardiogram, urinalysis, standard clinical laboratory tests, toxicology and pregnancy screenings, as well as recording of concomitant medication regimens. Participants are also assessed for contraindications to magnetic resonance imaging (MRI). They then undergo a psychiatric interview to confirm a diagnosis of MDD or BP according to Diagnostic and Statistical Manual for Mental Disorders, fifth edition (DSM-5) [23] criteria using the MINI International Neuropsychiatric Interview (MINI) Version 7.0.2 [24]. Depressive symptom severity is assessed using the MADRS, while lifetime history of suicidal ideation, behaviours, and attempts are assessed using the Columbia-Suicide Severity Rating Scale (C-SSRS) [26]. Absence of cognitive impairment is ascertained with the Montreal Cognitive Assessment (MOCA) [25]. An up-to-date Antidepressant Treatment History Form (ATHF) [27] is used to assess pharmacological treatment history (type, dose, duration). Participants provide sociodemographic information using standardized self-report forms and complete various self-report questionnaires assessing their pre-treatment psychiatric symptoms and quality of life.

Following the screening visit, eligible participants are formally enrolled in the study, randomized, and undergo baseline data collection, including a computerized cognitive battery, an MRI scan, and blood draws for genomic and molecular markers.

### Treatments

For both arms, whether treatment is initiated on an inpatient or outpatient basis depends on clinician judgment and logistical constraints at each participating site. ECT is administered according to standard of care with selection of specific treatment parameters (i.e., unilateral or bilateral electrode placement, and pulse duration) at the discretion of the treating psychiatrist. Each course of ECT generally starts with unilateral administration. According to patient response, physicians may opt to increase to bitemporal or bifrontal treatments. Selection of anaesthetic agents and muscle relaxants are at the discretion of the anaesthesiologist, with the exception of ketamine, which is not to be used as an anaesthetic agent during ECT.

Racemic ketamine hydrochloride is administered at a dose of 0.5 mg/kg diluted in 0.9% saline, over a 40-min period by an IV pump. Infusions are administered in ECT or post-anaesthetic care recovery rooms at each of the participating sites by study nurses or anaesthesiologist assistants under the supervision of a trained physician and with constant cardiorespiratory monitoring. Vital signs are monitored at 5-min intervals throughout each infusion and afterward until the return of preinfusion levels. Participants receiving ketamine are required to abstain from consuming grapefruit juice (a potent 3A4 cytochrome inhibitor that may slow ketamine elimination) on infusion days [28]. All participants must avoid taking anticonvulsants and benzodiazepines from the day preceding treatments as they attenuate ketamine response [29] and increase the seizure threshold, factors that can reduce the efficacy of ketamine and ECT.

At each treatment visit, clinical providers assess treatment response, side effects, adverse events and suitability for continued treatment. All reasonable efforts will be made to retain participants in the study without exerting undue pressure. Interventions may be discontinued based on clinical judgement in accordance with the risk-benefit ratio. Side effects are recorded using the clinician-rated Toronto Side Effect Scale (TSES) [30] and an adverse event log. A Data and Safety Monitoring Board (DSMB) has been assembled to monitor participant safety and treatment efficacy during the trial. This panel is comprised of three study independent experts: a psychiatrist, an anesthesiologist, and a statistician. Healthcare resource use occurring outside of the study, such as inpatient hospitalization, emergency room visits or outpatient consultations, is also documented at each visit. Finally, the estimated financial cost of administering each treatment is being calculated at each site.

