Speed of therapeutic effects is defined as the number of treatments required for participants to first meet antidepressant response criteria. A Kaplan-Meier survival analysis will be used to compare the mean number of required treatments for first response to ECT and ketamine during the randomized treatment phase. Side effect burden will be quantified by summing the total frequency and severity scores of the TSES administered after the final treatment during the randomized treatment phase. Mean total TSES scores for ECT and ketamine will be compared using an ANOVA (appropriate covariates will be included). Further, side effect profiles for each treatment will be derived by identifying the most common side effects reported in each arm of the trial (present in > 5% of participants). Treatment tolerability will be estimated via dropout rates. Finally, data from CNS Vital Signs will permit comparison of any cognitive side effects associated with ECT or ketamine (compared at the end of the randomized treatment phase). Level of health care utilization (estimated using average cost of treatment administration, number of days of inpatient hospitalization, and frequency of outpatient consultations) associated with ECT and ketamine will be compared using ANOVAs.

The main outcome in the maintenance phase will be time to relapse. Due to differences in the administration schedules of ECT and ketamine during maintenance, two parallel descriptive statistics will be outlined. For each treatment, mean time to relapse (loss of antidepressant response) will be estimated using Kaplan-Meier survival analysis.

While data from each analytical platform will be analyzed independently using the methods described herein and elsewhere [21], integration of data collected across platforms will also be carried out, and will be overseen by the CAN-BIND Data Science Advisory Team comprised of Principal Investigators, domain-specific informatics advisors, and operations support. In addition to conventional statistical approaches, machine-learning approaches will be applied particularly with regards to outcome prediction (i.e., response/non-response to ECT and ketamine at 3 or 4 weeks of treatment).

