This trial is comparing the efficacy, speed of therapeutic effects, side effect profiles, and health care resource use associated with ketamine and ECT. As a non-inferiority trial, we expect ketamine to exhibit similar efficacy rates as ECT yet with more rapid antidepressant effects, less side effects, and with substantially less cost and health care resource use. This study is among the first to directly compare these treatments using a randomized design, complementing an ongoing, large-scale, parallel-arm clinical trial comparing ketamine and ECT for treatment-resistant depression in the United States (the ELEKT-D trial) [53]. Unique aspects of our trial include the crossover design, where participants who do not respond to the first randomized treatment may crossover to receive treatment with the alternate strategy, longer-term treatment and follow-up through the maintenance phase, and the inclusion of individuals with either unipolar or bipolar depression. Ketamine and ECT are both effective treatments for BP [54, 55], although, the assessment of effective and long-lasting treatments in the context of BP has received substantially less attention than that of unipolar depression.

Another strength of the current study is that both treatment arms are administered under comparable conditions. There is a balanced frequency of treatment administration in each arm during the acute treatment phases. Moreover, ECT and ketamine treatments are administered in the same setting at each site, reducing variability that could arise due to numerous confounding factors. Finally, since treatments cannot be blinded from participants or from clinical and research staff, clinical ratings are being conducted by raters who are blind to the treatment and are otherwise not involved in the trial. This rigorous study design allows for the relatively unbiased evaluation of the antidepressant effects of ketamine relative to an active comparator, addressing a critical gap in this area.

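### Clinicians who know the arm choose the inpatient or outpatient start, and inpatient days are then compared between arms with no stated adjustment and an unclear definition of which days count

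*Protocol article*

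**What the plan says.** - **Setting.** The Treatments section states, for both arms, that "whether treatment is initiated on an inpatient or outpatient basis depends on clinician judgment and logistical constraints at each participating site". It gives no criterion. Table 1 admits inpatients and outpatients alike.
- **Order of events.** Under Procedure, randomization follows screening and comes before baseline collection and treatment. The article does not say that the intended setting is recorded before allocation.
- **Blinding.** The Discussion explains the use of blinded raters by noting that "since treatments cannot be blinded from participants or from clinical and research staff".
- **Outcome.** Data analyses defines utilization as "estimated using average cost of treatment administration, number of days of inpatient hospitalization, and frequency of outpatient consultations". These levels "associated with ECT and ketamine will be compared using ANOVAs", with no covariate named. In the same paragraph, the ANOVA of side-effect scores does promise covariates.
- **Data recorded.** The Treatments section says that what is documented at each visit is "Healthcare resource use occurring outside of the study, such as inpatient hospitalization, emergency room visits or outpatient consultations".
- **Role.** The Background places resource use in the primary objective, and the Discussion expects ketamine to need substantially less of it.

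**The concern.** The people who decide the setting know the arm, and the setting feeds straight into a compared outcome. Blinded raters protect the MADRS; nothing comparable protects inpatient days. If ECT and ketamine participants of equal clinical need were admitted at different rates, the difference would appear as a difference in resource use. The plan would hold no pre-allocation record with which to tell need from discretion.

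A second problem is what the measure contains. Collection is limited to use outside the study, while the analysis speaks of inpatient days with no such limit. Collection includes emergency visits, while the analysis list does not. At stake is whether the comparison of resource use, a named part of the primary objective, can be interpreted.

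**Working it through.** The plan gives no figure for inpatient share, length of stay or expected difference, so there is nothing to reproduce. The check has three parts.

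**1. Which sources can bias the comparison**

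| Source of inpatient days | Before or after allocation | Can it differ systematically by arm? |
|---|---|---|
| Already admitted at randomization | Before | No: balanced in expectation by 1:1 randomization |
| Site logistics common to both arms | Either | No: allocation is stratified by centre (Protocol overview) |
| Setting chosen once the arm is known, or logistics that differ by arm | After | Yes |

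**2. Size, if study-treatment admissions count**

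Inputs from the article: courses of 3 or 4 weeks (21 or 28 days), 100 analysed per arm, alpha 0.05. Assumptions not in the article: the gap in inpatient starts between arms, the share starting as inpatients, and a stay as long as the course.

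Spurious mean difference = gap × length of stay:
- 0 × 21 = 0
- 0.10 × 21 = 2.1 days; 0.20 × 21 = 4.2 days
- 0.10 × 28 = 2.8 days; 0.20 × 28 = 5.6 days

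A simulation put this through the planned one-way ANOVA. It used 100 per arm, 4,000 runs per scenario, a mean stay of 21 days (gamma, shape 4), no treatment effect on length of stay, and a base share of 20%, 40% or 60%:

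| Gap in inpatient starts | Mean difference (days) | ANOVA rejects at 0.05 |
|---|---|---|
| 0 points | about 0 | 4.5–5.1% |
| 5 points | 1.1 | 9–13% |
| 10 points | 2.1 | 21–31% |
| 20 points | 4.2 | 62–78% |

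The first row confirms part 1: with no arm-related gap, the test keeps its level.

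**Variance from entry status.** If 30% were inpatients at entry and each stayed 21 days, that alone gives an SD of 21 × √(0.3 × 0.7) = 9.6 days. With 100 per arm it contributes 9.6 × √(2/100) = 1.4 days to the standard error of the difference. Chance imbalance in inpatient share has a 95% range of ±1.96 × √(2p(1−p)/100), which is ±11 points at p = 0.2 and ±14 points at p = 0.4 or 0.5. The standard error already covers this; a covariate would remove much of it.

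**3. The two definitions side by side**

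| Item | Recorded (Treatments) | Analysed (Data analyses) |
|---|---|---|
| Inpatient stay | Only if outside the study | Inpatient days, no limit stated |
| Emergency visits | Yes | Not listed |
| Outpatient consultations | Only if outside the study | Frequency, no limit stated |

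If admissions for study treatment are outside the record, the comparison can omit a possibly large part of resource use. If they are inside it, the setting decision acts on the outcome as in part 2. On either reading, emergency visits are collected and then left out of the listed measure.

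**The case against.** **Arm-driven admissions may be real resource use.** If one treatment truly leads to more admissions, those days belong to that strategy, and the trial sets out to compare strategies. This stands. It rules out saying that such days reflect setting and not treatment. What remains is that need and discretion cannot be told apart afterwards.

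**Entry status and site logistics.** A reader might infer that these also distort the result. They do not: randomization and stratification by centre balance them in expectation, and they cost only precision.

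**Conjecture about staff.** A reader might infer that staff will admit more ECT participants because the Discussion expects ketamine to use less. Nothing in the article shows this. The route is open; its use is not established.

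**MADRS and drop-out.** A reader might extend the point to these. The article gives no basis for that, and MADRS raters are blinded.

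**Comparable conditions.** The Discussion says "both treatment arms are administered under comparable conditions", citing balanced treatment frequency and the same setting at each site. That may fairly describe where infusions and ECT sessions take place. It does not settle admission status, and it is not thereby wrong.

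**A condensed article.** Covariates and outcome definitions may be in a fuller document. This has force for the adjustment, although the article does mention covariates for the side-effect ANOVA and not for this one. It has less force for timing: an intended setting not recorded before allocation cannot be reliably reconstructed. The emergency-visit difference might also be condensation, since one list is of examples; it still needs reconciling.

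**Conclusion.** The point holds in limited form. A setting choice made with knowledge of the arm would enter the resource-use outcome directly, and the plan as described cannot separate clinical need from discretion. Pre-randomization admission status and shared logistics are a loss of precision that the stated ANOVA leaves unadjusted. The recorded and analysed measures do not match.

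The size is unknown. The range of 2.1 to 5.6 days rests on assumed gaps of 10 to 20 points and full-course stays. Zero is possible, and the figures apply only if admissions for study treatment are counted. The effect is confined to resource use; the primary response outcome and its sample size are untouched.

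**What to change.** 1. Record admission status and intended start setting before the allocation is released. This is a record only; it should not restrict later clinical choice. As the trial is under way, intended setting can be captured only for participants not yet randomized.
2. Adjust the resource-use comparison for pre-randomization inpatient status and centre.
3. Reconcile the Treatments and Data analyses sections: count all inpatient days in the randomized phase, and report days admitted for study treatment separately from other days.
4. Add the emergency visits already recorded to the utilization measure.

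The cost is one form field and slightly more analysis. Items 2 to 4 can be settled in the analysis plan, but if data collection has left out admissions for study treatment, item 3 also needs those days to be retrieved.

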### Treatment schedule

#### Randomized treatment phase

For participants receiving ECT, the number of treatments (9 or 12) is determined by the treating physician. For the ketamine arm, the number of treatments is determined by participants’ antidepressant response as assessed using the MADRS. Participants achieving remission (MADRS ≤10) after 9 ketamine infusions exit the randomized treatment phase and are eligible to enter the maintenance phase (Fig. 1). Participants receiving ketamine who achieve an antidepressant response but not remission after 9 treatments receive an additional 3 infusions (12 treatments total). In both treatment arms, non-responders (< 50% MADRS decrease or a score ≥ 22) after 3 weeks may crossover to receive a full course of treatment with the alternative strategy. Responders after 12 treatments may move on to the maintenance phase.

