### Assessments

#### Clinical platform

Participants in both arms are clinically assessed on an identical schedule. Clinical raters receive standardized training in the administration of measures of interest, and are assessed for inter-rater reliability. They remain blind to treatment arm and are not otherwise involved in the study, while participants are instructed not to disclose their treatment arm during ratings. On visits consisting of both clinical scales and treatment, clinical ratings are administered prior to treatment. Clinical scales are listed in Table 2.

**Table 2 Tab2:** Clinical assessments

*Clinician-Administered Assessments*	
Mini International Neuropsychiatric Interview (MINI)	
Montgomery-Åsberg Depression Rating Scale (MADRS)	
Clinical Global Impression (CGI)	
Young Mania Rating Scale (YMRS)	
Columbia-Suicide Severity Rating Scale (C-SSRS)	
Toronto Side Effects Scale (TSES)	
Montreal Cognitive Assessment (MOCA)	
CNS Vital Signs (CNS-VS), Computerized neurocognitive battery	
*Self-Report Assessments*	
Patient Health Questionnaire (PHQ-9)	
Generalized Anxiety Disorder 7-item scale (GAD-7)	
Quality of Life, Enjoyment and Satisfaction Questionnaire-short form (Q-LESQ-SF)	
Dimensional Anhedonia Rating Scale (DARS)	
Medical Outcome Study - short Form 36 (SF-36)	
Drug Abuse Screening Test (DAST-10)	
Beck Scale for Suicide Ideation (BSS)	

The primary study outcome measure is response rates to randomized treatment determined through percent change in MADRS scores from baseline (pre-randomized treatment phase) to end of randomized treatment. The MADRS is a 10-item scale designed to measure depression severity administered by a blinded rater using the Structured Interview Guide for the Montgomery-Åsberg Depression Rating Scale (SIGMA) [31]. Additional assessments include the Clinical Global Impression, Severity and Improvement Scales (CGI-S and CGI-I) [32], the C-SSRS, and the Young Mania Rating Scale (YMRS) [33]. Clinical assessments are obtained prior to each treatment during the first week (i.e., thrice-weekly), and then at weekly intervals throughout the randomized treatment and crossover phases. When administration of these scales occurs at shorter time intervals than the validated measurement timeframe, symptoms are assessed for the time period since last treatment.

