### Data analyses

The primary outcome measure is the rate of antidepressant response (i.e., percentage of participants meeting antidepressant response criteria [≥ 50% reduction in MADRS scores from baseline and MADRS score < 22]) in each arm at the end of the randomized treatment phase. A total of 240 participants will be enrolled into the randomized treatment phase across the four recruiting sites. This will allow for a 20% drop-out rate (i.e., withdrawal of approximately 40 participants), resulting in a total sample of *N* = 200. For the primary efficacy analyses, a non-inferiority margin of 20% was selected based on clinical judgment. Thus, a sample of 200 participants (*N* = 100/treatment arm) is required to be 90% certain that the upper limit of a one-sided 95% confidence interval will exclude a difference in favour of the ECT group of more than 20%. Secondary efficacy outcomes will include percent change in MADRS scores from baseline to the end of the randomized treatment phase, and remission rates (MADRS score ≤ 10). Response and remission rates will also be assessed for the crossover phase. Clinical scores will be analyzed using linear mixed models (appropriate covariates, such as site, will be included, as needed). Categorical outcomes (response/remission) will be examined using χ^2^ tests. The alpha will be set at 0.05.

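### End-of-phase remission is scored over two looks for ketamine under a stated MADRS rule, but not for ECT unless physicians happen to follow the same rule; a week-3 comparison should stand beside it

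*Protocol article*

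**What the plan says.** The Randomized treatment phase section gives the two arms different rules for when the phase ends.

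- **Ketamine, first look.** Those with a MADRS of 10 or less "after 9 ketamine infusions exit the randomized treatment phase and are eligible to enter the maintenance phase", and so count as remitters at that rating.
- **Ketamine, second look.** Those "who achieve an antidepressant response but not remission after 9 treatments receive an additional 3 infusions (12 treatments total"), after which they are rated again.
- **ECT.** "For participants receiving ECT, the number of treatments (9 or 12) is determined by the treating physician". The section ties only the ketamine number to the MADRS.
- **Both arms.** "non-responders (< 50% MADRS decrease or a score ≥ 22) after 3 weeks may crossover" to the other treatment, so a week-3 MADRS rating is needed in both arms.

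The Clinical platform section says of the MADRS raters: "They remain blind to treatment arm and are not otherwise involved in the study". It also puts both arms on one assessment schedule, weekly after the first week.

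Data analyses states: "Secondary efficacy outcomes will include percent change in MADRS scores from baseline to the end of the randomized treatment phase, and remission rates", with remission defined as a MADRS of 10 or less. Categorical outcomes are compared by chi-square at alpha 0.05. Response at the end of the randomized phase is the primary outcome.

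**The concern.** In the ketamine arm the phase stops on the very outcome that is later compared. A week-3 score of 10 or below is banked and cannot be lost. A responder just above 10 gets another rating that can only add to the remission count. An ECT participant whose course length is chosen on other grounds is scored once, after session 9 or session 12. If that participant would have scored 10 or below at week 3 but continues to 12, the remission can be lost.

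Ratings carry error, so the best of two looks yields more scores at or below a threshold than one look does, even when nothing has changed in the patient. At stake is how to read a ketamine advantage in remission: part of it could come from the scoring rule and not from the treatment.

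**Working it through.** **The plan's own figure.** The article gives no expected remission rate, so there is none to reproduce. The 100 per arm is consistent with its stated inputs. With margin 0.20, one-sided alpha 0.05, power 90% and 65% response in both arms (my choice: the midpoint of the 50–80% quoted for ECT in the Background), n = (1.645 + 1.282)² × 2 × 0.65 × 0.35 / 0.20² ≈ 97.5, or 98 per arm. I use 100 below.

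**Direction, by algebra.** Let y9 and y12 be the ratings after treatments 9 and 12.

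- Ketamine remission = P(y9 ≤ 10) + P(responder at 9, y9 > 10, y12 ≤ 10).
- ECT remission, if course length is unrelated to the score, = P(y9 ≤ 10) or P(y12 ≤ 10). These are equal when there is no true change.
- Excess for ketamine = P(responder at 9, y9 > 10, y12 ≤ 10). This is zero without rating error and positive with it.
- Ketamine response = P(responder at 9) − P(responder at 9, y9 > 10, non-responder at 12). Against ECT read once, the same rule therefore lowers ketamine response.

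**Size, by simulation (first model).** These inputs are assumed because the article does not give them: baseline MADRS mean 34, SD 5, cut at the entry floor of 26; true proportional improvement normal with mean 0.45 to 0.60 and SD 0.30, giving 44–63% response; rating-error SD 2 to 4. The arms are identical, with no true change from week 3 to week 4.

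| Setting | Ketamine minus ECT, remission |
|---|---|
| Independent errors | 3.0 to 6.4 points |
| Error correlation 0.5 one week apart | 2.2 to 5.0 points |
| ECT physicians' judgement shares part of the visit's fluctuation | 1.8 to 4.3 points |
| Both of the last two | 1.5 to 3.5 points |

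One example with independent errors, error SD 3 and 56% response: 37.7% v 32.7%, a difference of 5.0 points. With independent errors and 100 per arm, the nominal two-sided 5% test rejects in about 8–15% of trials, and 92–99% of those rejections favour ketamine.

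**A second score model.** True end score has mean 16, SD 9; baseline has mean 34, SD 4, floored at 26.

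| Error SD | Ketamine | ECT, one look | Difference |
|---|---|---|---|
| 0 | 27.0% | 27.0% | 0 |
| 2 | 31.5% | 27.6% | 3.9 |
| 3 | 33.5% | 28.1% | 5.4 |
| 4 | 35.2% | 28.9% | 6.3 |

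With a true end score of mean 14, SD 8, the difference is 4.8 to 7.7 points over error SD 2 to 4 (38.4 v 33.6% up to 42.4 v 34.7%).

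**Dependence on ECT practice** (mean 16, SD 9, error SD 2; ketamine 31.5% throughout):

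- Physician judges with error independent of the rater's: ECT 27.5%.
- Physician applies the ketamine rule to the same blinded score: ECT 31.5%, no excess.
- The same, and also continues every week-3 non-responder: ECT 31.7%, slightly reversed.

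**Response, the primary outcome.** In the first model, ketamine response is 3.9 to 6.7 points below ECT read once at week 3. In the second (error SD 2) it is 50.7% v 55.3%. That gap nearly vanishes (50.7% v 50.6%) if ECT counts only participants who respond at 9 and again at 12.

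**At a common week-3 look.** Both arms give 27.6% in the second model at error SD 2, a difference of zero.

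**The case against.** The strongest reply is that scoring ECT at one look is an inference. The article does not say how the physician chooses 9 or 12. The Treatments section has providers judge response and suitability to continue at every treatment visit, and lets electrode placement change with response. ECT courses may therefore also stop when the patient is well. This stands as a limit. The artefact shrinks as ECT decisions move closer to the blinded score, and disappears if they follow it exactly. It does not dispose of the point, because no such link is stated and the article does not say that providers see the ratings. If half the ECT participants were managed by the ketamine rule, 1.5 to 3.3 points would remain.

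Second, the size rests on assumed error. The structured interview, rater training and reliability checks argue for the lower end, and errors a week apart may be correlated. The range above allows for correlation.

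Third, true gains in week 4 could favour ECT participants who go on to 12. With a true 2-point gain in both arms, ketamine still leads by 1.0 to 2.8 points if all ECT participants go to 12, and by 8.7 to 11.4 points if all stop at 9. The second figure includes a real difference in treatment received.

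Fourth, the full protocol or analysis plan, not shown, may already set a common scoring time. If so, the point is met. The concern here is the arm-specific rule that the article does state, not a missing detail.

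A reader might also infer that rating noise is bound to give ketamine the higher remission rate, or that the trial as a whole tilts toward ketamine. The article supports neither. The first depends on unstated ECT practice, and on the primary outcome the same rule can count against ketamine.

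**Conclusion.** The concern holds in conditional form. The article states an outcome-triggered stop with a second look for ketamine and none for ECT, then compares remission between the arms. Unless ECT physicians in effect follow the same rule on the same score, equal treatments would show a ketamine remission excess of roughly 2 to 6 points. That assumes no true change from week 3 to week 4, rating-error SD 2 to 4 and error correlation 0 to 0.5. Some settings fall outside this range: 1.5 points when correlated errors and partly shared physician judgement combine, and 7.7 points in the second score model with independent errors.

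Remission is secondary and has no stated margin or power, so the primary conclusion does not rest on it. The end-of-phase comparison remains a legitimate comparison of the completed courses. It cannot by itself support a claim that ketamine gives more remission.

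**What to change.** In Data analyses, keep the end-of-phase remission comparison and add three statements:

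1. Remission and response will each also be compared between arms at the week-3 MADRS rating, the last before the ketamine exit rule acts. Reporting both at the same visit keeps remitters a subset of responders.
2. End-of-phase remission for ketamine is cumulative over two ratings, because of the exit rule.
3. An end-of-phase remission advantage for ketamine will not be claimed unless the week-3 comparison supports it.

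Week 3 should not replace the end-of-phase comparison. It compares 9 treatments and not the completed courses, and the Discussion expects ketamine to act faster, so an early look alone could cut off later ECT gains.

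The cost is one extra analysis on ratings already collected in both arms. The downside is that the week-3 comparison misses gains made in week 4 in either arm. No treatment rule needs to change.
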